**Methods:**

We use a stepped-wedge cluster randomized controlled trial (SW-RCT). The PATINA algorithm and decision support tool will be implemented in 20 individual area home care teams across three Danish municipalities (Kerteminde, Odense and Svendborg). The study population includes all home care receiving community-dwelling citizens aged 65 years and above (around 6500 citizens). An algorithm based on home care use triggers an alert based on relative increase in home care use. Community nurses will use the decision support tool to systematically assess health related changes for citizens with increased risk of acute hospital admission.

The primary outcome is acute admission. Secondary outcomes are readmissions, preventable admissions, death, and costs of health care utilization. Barriers and facilitators for community nurse’s acceptance and use of the algorithm will be explored too.

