## Methods/design

### Study design

The study is designed as a multicenter randomized controlled trial using a stepped-wedge cluster design (Fig. 1) to implement and test the ‘PATINA algorithm and decision support tool’ in three Danish municipalities. Three stages will sequentially be rolled-out across the area home care teams in the three municipalities (described later); usual care exposure; intervention implementation and intervention exposure, followed by a one month and three-month post intervention follow-up. The timing of the one-way crossover from usual care to intervention exposure is randomly allocated during the intervention period (June 1, 2020 – May 31, 2021).

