### Study procedures

#### Randomization and implementation

The stepped-wedge design allows all 20 area home care teams across the three municipalities to receive the intervention, but at different time points according to randomization. Following the time schedule, a new area home care team is included in Kerteminde Municipality approximately every 12 weeks, in Svendborg Municipality every six weeks, and in Odense Municipality every four weeks (Fig. 1). The computer-generated stepwise randomization is carried out by a statistician from Open Patient data Explorative Network (OPEN), Odense University Hospital, Region of Southern Denmark.

All three municipalities are made aware of the randomization procedure prior to study start. However, the starting date for the intervention exposure will not be announced until four weeks prior to implementation start.

In this study it is not possible to blind neither nurses or other health care professionals, nor the management in each municipality. However, nurses and the management are instructed only to talk about the project with coworkers within their own area home care team, and not with colleagues in other teams.

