***Secondary outcomes***		
Outcome 2	Preventable admission	Preventable admission after being identified at risk by the algorithm
Outcome 3	Readmission (30-days)	Readmission to a Danish hospital within 30 days from a hospital discharge
Outcome 4	Outpatient contacts	Proportion of contacts to outpatient clinics after being identified at risk by the algorithm
Outcome 5	Primary care physicians contacted	Contacts to a primary care physician after being identified at risk by the algorithm
Outcome 6	Death (90-days)	Proportion of diseased citizens identified at risk by the algorithm within 90 days

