#### Statistical analyses

Data management and statistical analyses will be carried out using SAS version 9.4 software (SAS Institute Inc., Cary, NC, USA) and STATA version 16 (StataCorp LLC, Texas, USA). The analyses will be supplemented by modelling and graphics using “R” software (Version 3.6.1) [25].

Data analyses will be conducted according to intention-to-treat principles and include all eligible patients with available outcome data. The analyses will be conducted according to the randomization schedule. Citizens’ characteristics will be reported using numbers/percentages, means (SD), and medians [IQR]. Differences between the intervention and control groups will be calculated using chi2 tests, Student’s t-test, or Kruskal-Wallis test, as appropriate. The statistical significance threshold for all tests will be set to *P* < 0.05.

When presenting the results of our study we will use suiting EQUATOR network guidelines such as the CONSORT 2010 statement [40] with the extension for stepped wedge cluster randomized trials [41].

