#### Analysis of primary and secondary outcomes

Outcomes are shown in Table 2. The primary outcome, proportion of acute admission, will be analyzed using co-variance, repeated measure analysis and logistic regression. A key event is the switch from the usual care to intervention phase. We will treat the intervention regression coefficient as a slopes term to account for potential differences in intervention effects across area home care teams. The analyses will be adjusted for relevant confounders such as age, gender, co-morbidity, functional level and frailty.

For secondary outcomes (Table 2) 2, 3, 4, 5 and 6 we will use logistic regression to analyze occurrence of event. Citizens, who relocate to another municipality, move into a care home, or die during the study period will be excluded from the analyses. Models for acute admission will be used and the incidence of acute admission will be analyzed using logistic regression. The analysis will be adjusted for confounding factors such as age, gender and co-morbidity. We will stratify the analyses by municipalities and area home care teams to control for differences between these.

When analyzing readmission between the intervention and control group we will focus on both the 30-day readmission rate (outcome 3) and 90-day readmission rate (outcome 4). The index-admission will be defined as any admission to a Danish hospital during the study period. Citizens with multiple hospital admissions can have several index admissions but only one readmission per index admission.

Changes in citizens health service utilization (outcome 7, 8 and 9) will be evaluated in order to assess changes in costs of care and treatment in the primary and secondary health care sector. We will analyze the average cost per citizen, as well as analyses of the change in costs in primary and secondary health care. We will also analyze the costs of implementing the PATINA algorithm and decision support tool (outcome 10). This will be done by summing up the time spent on project related activities by both nurses and project coordinators in each municipality. The costs of implementing the algorithm will be reported as the total cost of the intervention with a 95% confidence interval.

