### Study status

After achieving the necessary ethical and governance approvals the study began including area home care teams in the three Danish municipalities on the June 1, 2020 with an expected end date of May 31, 2021. The study start was postponed from April 1, 2020 (two months) due to COVID-19 and has run continuously since.

The study is registered at ClinicalTrials.gov (NCT04398797) and will be updated accordingly.

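### Citizens who die in the study period are excluded from the analyses of outcomes 2 to 6, yet outcome 6 is 90-day death

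*Protocol article*

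**What the plan says.** In the protocol article, the section Analysis of primary and secondary outcomes gives the method for the secondary outcomes: "For secondary outcomes (Table 2) 2, 3, 4, 5 and 6 we will use logistic regression to analyze occurrence of event". The next sentence sets the analysis population: "Citizens, who relocate to another municipality, move into a care home, or die during the study period will be excluded from the analyses". No exception for any outcome follows.

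Table 2 labels outcome 6 as 90-day death and defines it as "Proportion of diseased citizens identified at risk by the algorithm within 90 days" (the first noun is evidently meant to be deceased). The abstract also names death: "Secondary outcomes are readmissions, preventable admissions, death, and costs of health care utilization".

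The section Statistical analyses states the general principle: "Data analyses will be conducted according to intention-to-treat principles and include all eligible patients with available outcome data".

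The term study period is not defined. Study status gives the study "with an expected end date of May 31, 2021", while Study design describes an intervention period ending on that date, "followed by a one month and three-month post intervention follow-up".

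**The concern.** The rule removes from the data the very events that outcome 6 counts. A citizen who died within 90 days of a flag has a fully observed value for that outcome, so the intention-to-treat statement would keep that citizen and the exclusion rule would not.

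For outcomes 2 to 5 the rule selects on what happens after randomisation and after the flag. A citizen flagged in month 1, with a complete 30-day readmission record, is deleted for a death in month 11. Those removed are likely to be the sickest. Death and care-home entry are also events that the intervention could change, so the selection can itself depend on treatment.

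The stepped-wedge design adds a further problem. Control time comes first, so control-phase flags have more calendar time left in which the citizen can die or move. The share removed therefore differs by phase even if the intervention has no effect on mortality.

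**Working it through.** The article gives no mortality figure, so there is no stated number to reproduce. The contradiction follows from the text; the sizes below rest on labelled assumptions.

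**Inputs from the article.** The intervention period is 1 June 2020 to 31 May 2021 (365 days, 52 weeks), with follow-up to three months. New teams start "every 12 weeks, in Svendborg Municipality every six weeks, and in Odense Municipality every four weeks", with 3 teams in Kerteminde, 7 in Svendborg and 10 in Odense. The populations over 65 are 6142, 14,206 and 35,811 (Table 1). The planning admission risks are 12% and 10.8%.

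**Assumptions.** Flags are spread evenly over the year and deaths evenly over the 90 days after a flag. The first team in each municipality crosses over either at week 0 or one step in.

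**1. Outcome 6, study period including follow-up.** June to August has 30 + 31 + 31 = 92 days, so even a flag on 31 May 2021 has its 90-day window inside the period. Every 90-day death is excluded. There are 0 events and no logistic model can be fitted.

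**2. Outcome 6, study period ending 31 May 2021.** With r days left at the flag, the share of the 90-day window beyond the end is (90 − r)/90 for r < 90 and 0 otherwise. Averaged over the year this is 45/365 = 0.123.

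| Assumed 90-day mortality | Deaths per 1,000 flagged | Deaths left by the rule |
|---|---|---|
| 3% | 30 | 3.7 |
| 6% | 60 | 7.4 |
| 10% | 100 | 12.3 |

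The remaining deaths all come from flags after about week 39 (275/7 = 39.3). The last crossovers are:

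- Kerteminde: week 2 × 12 = 24, or 36 with the later start
- Svendborg: week 6 × 6 = 36, or 42
- Odense: week 9 × 4 = 36, or 40

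With the earlier start, no control-phase flag falls late enough. With the later start, only the last Svendborg and last Odense teams contribute, and they supply 0.2% of the retained deaths (teams weighted by population over 65) or 0.3% (teams weighted equally). There is no control group for mortality.

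**3. Outcomes 2 to 5, share of flags removed for death alone.** For a flag with t weeks left, the removed share is 1 − exp(−μt), with μ = −ln(1 − annual mortality)/52, averaged over all flags in the phase. The mean time left is 38-39 weeks for control-phase flags and 17-19 weeks for intervention-phase flags.

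| Assumed annual mortality | Control-phase flags removed | Intervention-phase flags removed |
|---|---|---|
| 10% | 7-8% | 3-4% |
| 15% | 11-12% | 5-6% |
| 25% | 19-20% | 9-10% |

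Check at 15%: μ = 0.1625/52 = 0.003125. At t = 38.5 the share is 1 − exp(−0.120) = 11.3%; at t = 18 it is 1 − exp(−0.056) = 5.5%.

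**4. What survivor-only analysis does to an admission risk.** Survivor risk = (p_adm − p_death × P(adm | death)) / (1 − p_death). The article gives planning risks only for acute admission, so those are used (true difference 1.2 percentage points). P(adm | death) is assumed to be 0.7.

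- Mortality 6% in both phases: 0.078/0.94 − 0.066/0.94 = 8.30% − 7.02% = 1.3 points.
- 6% control, 4% intervention: 0.078/0.94 − 0.080/0.96 = 8.30% − 8.33% = −0.04 points.
- 4% control, 6% intervention: 0.092/0.96 − 0.066/0.94 = 9.58% − 7.02% = 2.6 points.

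With P(adm | death) between 0.5 and 0.9, these scenarios span −0.5 to 3.0 points. An intervention that also saved lives could thus show no benefit on admission, and one that cost lives could show a doubled benefit.

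**The case against.** **Scope.** The exclusion sentence says only that it applies to the analyses, and the sentence after it turns to acute admission. It may have been meant for the admission models, where death and departure end follow-up. The authors plainly intend to analyse death and probably did not mean to empty outcome 6. That is likely true of the intention, but the sentence just before names outcome 6 and nothing exempts it. If the rule does reach the admission models, the primary outcome is affected as well. Exempting outcome 6 would still leave outcomes 2 to 5 restricted by future events.

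**Relocation and care-home entry.** These citizens leave the population of community-dwelling home-care recipients. Ending their follow-up at that point could be defended, so the intention-to-treat conflict is weaker here than for death. This stands in part: it supports stopping follow-up at the move, but not deleting what was observed before it.

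**Register coverage of death.** The Data collection section lists the Civil Registration System without naming date of death. That is correct, but both outcome 6 and the exclusion rule presuppose that the study knows who died.

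**Size of the imbalance.** A constant hazard may be wrong, since the algorithm picks up recent deterioration. At 15% annual mortality with half to two-thirds of the hazard in the first 13 weeks, the losses are about 12-14% against 7-10%, a ratio of 1.4-1.7 in place of about 2. In addition, the Discussion promises adjustment for time. Citizens flagged in the same week have the same time left, so such adjustment would absorb much of the imbalance that arises from flag date alone. Both points reduce the effect on the estimates for outcomes 2 to 5. Neither helps outcome 6, and time adjustment does not remove selection that arises because the intervention changes death or care-home entry.

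**Conclusion.** The concern holds and must be fixed. As written, a named secondary outcome cannot be estimated: no deaths remain under one reading of the study period. Under the other about 12% remain, with at least 99.7% of them from the intervention phase. The 12% assumes even flagging; the contradiction itself needs no assumption.

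Outcomes 2 to 5 are restricted to citizens selected by later events, against the stated intention-to-treat principle. The unadjusted loss through death is about twice as high in the control phase at a constant hazard (11-12% against 5-6% at an assumed 15% annual mortality) and about 1.4 to 1.7 times as high with a front-loaded hazard. The resulting bias in the treatment estimates depends on mortality and on the link between death and admission, neither of which the article gives. The figures in step 4 therefore illustrate that bias and do not estimate it.

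**What to change.** Delete the exclusion sentence and replace it with the following rules.

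- Analyse all citizens flagged by the algorithm, by the phase of their team at the flag date.
- Count every death within 90 days of the flag as an event in outcome 6.
- For the admission, readmission and contact outcomes, keep each citizen in the analysis until death and treat death as a competing event. A composite of acute admission or death can serve as a supportive analysis.
- Keep citizens who relocate or enter a care home, using the national registers that the Data collection section already links.
- Define the end of the study period and of each outcome window.
- If wanted, keep the analysis of citizens who survived and stayed as a sensitivity analysis, labelled as such.

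The cost is a short rewording of the protocol and analysis plan and slightly more analysis work. No new data are needed.

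### Excluding citizens who die removes all, or about 88%, of the events of outcome 6 (90-day death) and selects outcomes 2 to 5 on survival

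*Protocol article*

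**What the plan says.** Four statements in the protocol article bear on this point.

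- **Outcome 6 (Table 2, secondary outcomes)** is 90-day death, measured as "Proportion of diseased citizens identified at risk by the algorithm within 90 days". The word *diseased* evidently stands for deceased.
- **Method (Analysis of primary and secondary outcomes):** "For secondary outcomes (Table 2) 2, 3, 4, 5 and 6 we will use logistic regression to analyze occurrence of event". Outcome 6 is named.
- **Exclusion (the next sentence of that section):** "Citizens, who relocate to another municipality, move into a care home, or die during the study period will be excluded from the analyses". No outcome is exempted.
- **Analysis population (Statistical analyses):** "Data analyses will be conducted according to intention-to-treat principles and include all eligible patients with available outcome data".

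The article does not define the study period. Study status describes the study as running from 1 June 2020 "with an expected end date of May 31, 2021". Study design describes the roll-out as "followed by a one month and three-month post intervention follow-up". The exclusion could therefore stop at the end of May 2021 or run through the follow-up.

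**The concern.** A death within 90 days of the flag is the event that outcome 6 counts, and dying during the study period is the ground for removal. The two rules stand next to each other and apply to the same analyses. A flagged citizen who dies within 90 days has an observed outcome 6, so removal also conflicts with the promise to "include all eligible patients with available outcome data".

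Outcome 6 is the trial's only mortality outcome. The intervention aims to reduce acute admissions, which the article itself says can be lifesaving. A mortality comparison without the deaths cannot reassure anyone on safety.

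For outcomes 2 to 5, being analysed depends on surviving to the end of the study period. Survival comes after randomisation and the intervention may affect it. Preventable admissions, readmissions and contacts that occurred before a death are dropped with the citizen.

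**Working it through.** **Figure to reproduce.** There is none. The article gives no mortality rate, event count or power for outcome 6; its power calculation concerns acute admission only.

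**Inputs from the article**
- Outcome 6 window: 90 days from the flag.
- Intervention period: 1 June 2020 to 31 May 2021, 365 days (52 weeks = 364 days in the schedule arithmetic).
- Follow-up: one month and three months after the intervention.
- Schedule (Fig. 1 legend): 3 teams every 12 weeks, 7 every 6 weeks, 10 every 4 weeks.

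**Assumptions.** Flags are uniform over the year, deaths are uniform over the 90 days after the flag, and teams have equal weight. The first team in each municipality switches either on day 0 or after one interval.

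**Step 1: share of outcome 6 events removed.** A 90-day death stays in only if it falls after the study period ends.

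| Study period ends | Share retained | Share removed |
|---|---|---|
| 31 May 2021 | 45/365 = 12.3% | 87.7% |
| After one-month follow-up | (60²/(2×90))/365 = 20/365 = 5.5% | 94.5% |
| After three-month follow-up | 0 | 100% |

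Here 45 is the mean of a uniform death time over 90 days. Simulation on the schedule gave 87.6% for the first row. Exponential death times with an assumed one-year mortality of 10% to 30% gave 87.7% to 87.8%. The result depends more on the timing of flags: first flags bunched early in the year would raise the share removed, and flags bunched late would lower it.

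**Step 2: where the retained events fall if the period ends on 31 May 2021.** Only flags after day 364 − 90 = 274 can contribute. The retained amount over all teams is 20 × 45 = 900 team-days.

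- *First switch on day 0.* The last switches are on days 168, 252 and 252, all before day 274, so no control-phase death is retained. Control team-days are 84×(0+1+2) + 42×(0+…+6) + 28×(0+…+9) = 252 + 882 + 1260 = 2394. Intervention team-days are 7280 − 2394 = 4886. Retained share under intervention: 900/4886 = 18.4%.
- *First switch after one interval.* The last switches are on days 252, 294 and 280. Control contribution: 20²/180 + 6²/180 = 2.2 + 0.2 = 2.4. Control team-days are 84×6 + 42×28 + 28×55 = 504 + 1176 + 1540 = 3220, leaving 4060 under intervention. Retained shares: 2.4/3220 = 0.07% in control and (900 − 2.4)/4060 = 22.1% under intervention.

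At least 1 − 2.4/900 = 99.7% of the retained events are therefore intervention-phase.

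**Step 3: the crude contrast with no true effect.** With true 90-day risk p in both phases and retained share r, the analysed risk is about p·r / (1 − p(1 − r)), counting only removals through 90-day deaths. The article gives no p, so the values below are assumed.

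| Assumed p | Control | Intervention |
|---|---|---|
| 3% | about 0% | 0.6–0.7% |
| 5% | about 0% | 1.0–1.2% |
| 10% | about 0% | 2.0–2.4% |

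**Step 4: outcomes 2 to 5.** The direction can be reasoned but not sized. Control-phase flags come earlier on average, so those citizens have longer in which to die and be excluded. The filter is thus unequal between phases even without a treatment effect.

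**The case against.** The strongest defence concerns what follows from the contradiction, since nothing in the article removes it.

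- **False signal of harm.** A reader might infer from Step 3 that the trial would report excess deaths under the intervention. The documents do not support that unconditionally. The Discussion says the analyses will adjust for clustering and for confounding by time. With equal mortality in both phases, whether a death survives the exclusion depends only on the flag date. Conditional on date there is no spurious effect, only almost no events in periods that contain both phases. The contrast also needs the study period to end on 31 May 2021; with follow-up included there are no events in either phase. What stands is that a comparison without time adjustment would mislead, and the confounders listed for the secondary outcomes do not include time.
- **A percentage loss for outcomes 2 to 5.** It is tempting to simulate how many admitted citizens would be dropped. Any such figure rests on assumed mortality, frailty and admission risks. Acute admission is outcome 1, and Table 2 gives outcomes 2, 4 and 5 no time window. Only the qualitative point stands.
- **Reach to the primary outcome.** The sentence after the exclusion turns to acute admission, so a reader might extend the rule to it. The text is unclear on this, and the point does not depend on it.
- **Drafting slip.** The authors may not have meant the rule for outcome 6. That is plausible, but outcome 6 is named in the preceding sentence without exception, and outcomes 2 to 5 are affected either way.

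**Conclusion.** The exclusion of citizens who die is wrong as written. It removes 100% of outcome 6 events if the study period includes the three-month follow-up and about 88% if it ends on 31 May 2021, given evenly spread flags. On the narrow reading, at least 99.7% of what remains is intervention-phase under the documented schedule and equal team weights. No reading leaves outcome 6 usefully estimable, and time adjustment cannot restore deleted events. The rule also contradicts the intention-to-treat statement.

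For outcomes 2 to 5, the rule selects on survival after randomisation and discards events before death, by an amount the documents do not let one derive. The contradiction rests on the text alone; the 88% needs the stated assumptions, and the risks in Step 3 are illustrative.

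**What to change.** 1. Delete *or die* from the exclusion sentence.
2. Analyse outcome 6 in all flagged citizens, counting every death within 90 days of the flag, including deaths after 31 May 2021.
3. For outcomes 2 to 5, keep citizens who die and count their events up to death. The stated logistic regression on occurrence of an event allows this. A competing-event analysis is one acceptable option for a sensitivity analysis, not a requirement.
4. Define the study period, stating whether it includes the follow-up.

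The cost is a few words in the analysis section. No new data collection is needed: outcome 6 already requires death data, although the Data collection section does not name vital status among the register items it lists as examples.
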